#### Evaluating the effectiveness of ESD service provision

To investigate our study hypotheses, information about each ESD service collected by SSNAP in the 2015 post-acute organisational audit will be collated by the research team. This will include ESD team composition, capacity, workload, and organisational features, e.g. frequency of team meetings. ESD team models will then be analysed by comparing ESD service information with ESD consensus statements and national clinical guideline recommendations [2, 8, 17]. This will be the first step in the investigation of adoption of evidence-based core components, e.g. stroke specificity and multidisciplinary team composition. An ESD consensus score will be applied to each ESD team included in our multilevel modelling.

Additional variables in the model obtained from the 2016 SSNAP clinical data at the patient level will include age at admission, sex, pre-stroke independence, comorbidities, NIH Stroke Scale score on admission, type of stroke, and modified Rankin score at discharge from hospital [26, 27]. These reflect previously validated stroke case-mix models [28, 29]. Data variables at the ESD team level (in addition to the ESD consensus score) will include level of rurality and deprivation [30] as well as the grade/score of each discharging hospital as recorded by the SSNAP team (to account for the influence of the quality of inpatient care prior to ESD). A ‘team-size’ score will also be included (total whole time equivalent (WTE) units per member of staff). By including these ESD team-level ‘contextual variables’ in our analysis, we are assuming that they may not be homogeneous across the ESD teams and may impact upon service provision as well as patient outcomes. Moreover, multilevel modelling enables us to appreciate the variation in outcomes as a mixture of patient variability nested within ESD service provision variability. Effectiveness of ESD service provision will be measured with the following outcome variables: responsiveness (time from hospital discharge to first contact), rehabilitation intensity (total number of treatment days/total days with ESD), and stroke survivor outcome (modified Rankin Scale after ESD delivered).

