To achieve these objectives, we will seek to answer the following questions:What adopted models of ESD exist and how do these relate to evidence-based recommendations?Can realised benefits of implementing ESD be quantified by defined measures of effectiveness: reduction in length of hospital stay, responsiveness of the service, amount of rehabilitation delivered, and changes in patient dependency?What site-, model-, and patient-level characteristics influence effectiveness of ESD services?What are the cost consequences of adopted ESD models?What contextual elements influence whether ESD is implemented in the first place and how do they shape the model of service adopted?What are the perceived outcomes of implementing ESD from the perspective of service users, clinicians, managers, and commissioners and how are these achieved in practice?What are the conditions that contribute to the successful implementation and sustainability of ESD in practice?

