‘If members of an ESD service have to cover long travelling distances in a rural setting, then the team may respond by making effective use of communication at team meetings and increased coordination (timetabling), resulting in patient centred goal setting and increased intensity of rehabilitation provided’

Example of a countervailing CMO with unintended consequences

‘If members of an ESD service have to cover long travelling distances in a rural setting, this may place a burden of the team’s communication and coordination and result in patients receiving less therapy than patients in urban settings’

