#### Data collection and analysis

Work package 1 will involve analysis of historical prospectively collected SSNAP data from hospital and community providers across the East Midlands, West Midlands, East of England, and North of England strategic clinical networks. A key aim of WP1 is to investigate whether the degree to which an ESD service has adopted an evidence-based model is related to better patient care (measured by ESD responsiveness and rehabilitation delivered) and patient dependency (modified Rankin Scale) [26] as well as the influence of rurality of the ESD service location. Effects of ESD on length of hospital stay will also be investigated; however, this analysis will require a different calibration of the statistical model and will be dealt with separately. To conduct these analyses, we employ multilevel modelling as it is an appropriate technique when analysing outcome variables that are generated from a clustered/nested structure whereby the outcome under consideration is produced by patients in different ESD team/hospital settings.

The effectiveness of ESD will be measured with evidence-based metrics as defined by national clinical guidelines for stroke and that reflect outcome measures used in the original ESD trials [6, 7]. Measuring the effects that ESD teams have on their patients is a necessary first step to learning how ESD practices combine to generate differences between teams. Combining SSNAP clinical audit data at the patient level with post-acute organisational audit data at the ESD team level, we will attempt to measure the ‘true’ effects that ESD teams have on their patients by fitting two-level patients-within-teams multilevel models to patient and process outcomes where covariate adjustments are made for a range of patient and ESD team characteristics.

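### The only model described for responsiveness, intensity and modified Rankin gives the rurality effect at a fixed service model, so it can differ from the overall rural-urban difference

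*Protocol article*

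**What the plan says.** The protocol article, under Data collection and analysis, gives Work package 1 a key aim in two parts. One is whether adopting the evidence-based model is related to better care and lower dependency. The other is added as "as well as the influence of rurality of the ESD service location". The method is a two-level patients-within-teams model in which "covariate adjustments are made for a range of patient and ESD team characteristics".

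Evaluating the effectiveness of ESD service provision lists the covariates. "An ESD consensus score will be applied to each ESD team included in our multilevel modelling", and "Data variables at the ESD team level (in addition to the ESD consensus score) will include level of rurality and deprivation". The grade of the discharging hospital and a team-size score based on whole time equivalents are also included. No second covariate set is described for responsiveness, intensity or modified Rankin. The article does not say whether the overall or the direct influence of rurality is wanted.

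The causal order is set out elsewhere in the article:

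- The Background says that contextual influences work for or against evidence-based implementation, and one research question asks of contextual elements "how do they shape the model of service adopted".
- The Conceptual framework treats the core components as programme resources, which are part of the mechanisms, and says that conditions shape mechanisms.
- Table 1 puts rurality under Context. Team composition, a staff/patient ratio and team co-ordination stand under Mechanisms, ahead of Outcomes.

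**The concern.** One covariate set serves two questions that need different ones. For the effect of adopting the evidence-based model, rurality is a possible confounder and belongs in the model. For the influence of rurality, the consensus score is, on the article's own framework, a possible intermediate step. Holding it fixed removes whatever rurality does through the service model adopted.

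Suppose that rural teams deliver less therapy because they could not assemble the recommended team. A model that compares rural and urban teams with equal scores may then show little rurality effect, and a reader could conclude that location does not matter. The results feed the candidate programme theories, so the meaning of the coefficient needs to be clear.

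**Working it through.** The article states no sample size, number of teams, intraclass correlation or association between rurality, score and outcome. There is no planned figure to reproduce. **All path values below are assumptions.**

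**Identity.** In a linear model without interaction, let d be the effect of rurality not passing through the service model, a1 and a2 the effects of rurality on consensus score and team size, and b1 and b2 the effects of those two on the outcome (standardised, higher is better). Then:

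- overall effect = d + a1·b1 + a2·b2, estimated without the score and team size;
- coefficient in the planned model = d.

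**Numbers**, with b1 = 0.3 and b2 = 0.2 throughout:

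| Case | d | a1·b1 | a2·b2 | Overall | Planned model |
|---|---|---|---|---|---|
| 1. No path | -0.10 | 0 | 0 | -0.10 | -0.10 |
| 2. Score only | -0.10 | -0.4 × 0.3 = -0.12 | 0 | -0.22 | -0.10 |
| 3. Score only, no direct effect | 0 | -0.12 | 0 | -0.12 | 0.00 |
| 4. Score and team size | -0.10 | -0.12 | -0.4 × 0.2 = -0.08 | -0.30 | -0.10 |
| 5. Both, no direct effect | 0 | -0.12 | -0.08 | -0.20 | 0.00 |
| 6. Both, opposing direct effect | +0.10 | -0.12 | -0.08 | -0.10 | +0.10 |
| 7. Both, weaker paths | +0.10 | -0.2 × 0.3 = -0.06 | -0.2 × 0.2 = -0.04 | 0.00 | +0.10 |
| 8. Rural teams higher on both | -0.10 | 0.4 × 0.3 = +0.12 | 0.3 × 0.2 = +0.06 | +0.08 | -0.10 |

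A simulation of all cases except case 3 (2,000 teams of 50 patients, intraclass correlation 0.10, all assumed) agreed with the formula to within about 0.02. Case 3 is arithmetic only.

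**Reading.** The two columns agree only when the products a·b are zero or cancel. Case 2 needs the consensus score alone and shows a coefficient less than half the overall effect (0.10/0.22 = 45%). Reversal (cases 6 and 8) needs a direct effect that opposes the path through the service model. The Conceptual framework allows rurality to act in either direction through mechanisms, so opposing signs are conceivable, but nothing in the article shows that they occur.

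**Which variables are mediators.** The case for the consensus score is the stronger one: it measures adoption of core components, which the article calls resources within the mechanisms. Team size is less clear. The model description groups it with contextual variables, while Table 1 lists a staff/patient ratio, which is a different quantity, under Mechanisms.

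**The case against.** The strongest reply is that the article lists covariates and does not say how rurality will be interpreted. A reader might infer that the rurality answer will come only from the fully adjusted coefficient. The text does not say so, and an analysis plan that is not shown could enter variables in stages. That limits the point to the one model described.

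The direct effect may also be what is wanted. One research question asks which site-, model- and patient-level characteristics influence effectiveness, and a joint model is an ordinary answer to that. Travel over a large area could matter even at a fixed service model. This stands: the adjusted coefficient is a legitimate quantity. If rural teams are 0.8 SD higher on the score, the score effect is 0.2 per SD and the direct effect is -0.16, the overall effect is -0.16 + 0.8 × 0.2 = 0.00. The planned model's -0.16 is then a true direct effect, and it would be wrong to call it false harm.

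Three further readings go beyond the documents:

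- **That the effect will vanish or change sign.** This depends wholly on assumed paths, and with no path nothing changes.
- **That the facilitatory rural example proves mediation through the score.** It says "the team may respond by making effective use of communication at team meetings and increased coordination (timetabling", which is a team response, and the article assigns responses mainly to the qualitative data. Information on teams does include "organisational features, e.g. frequency of team meetings", but the items that make up the score are not given.
- **That the coefficient determines the case study sites.** Work package 2 samples urban and rural sites purposively, which can be done from a site's classification. Its qualitative work and the triangulation also examine rurality.

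What remains is that the aim is stated, the only model described conditions on a variable that the framework places after context, and the resulting term is not labelled.

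**Conclusion.** The point holds in a limited form. The planned model suits the adoption question. Its rurality term answers a narrower question than the stated aim suggests, because it excludes any effect passing through adoption of the core components. It can understate the overall rural-urban difference and, under some assumed values, reverse it.

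The actual size cannot be known from the documents. In the assumed cases it runs from nil (case 1) to a shift of 0.20 standardised units (cases 4 to 6). The conclusion rests on the consensus score being influenced by rurality and in turn affecting the outcome, which the framework treats as possible and which the audit data can partly check. Team size adds to the concern only if it too is taken as a mechanism.

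**What to change.** 1. State whether the overall or the direct influence of rurality is meant.
2. For each of the three outcomes, also fit rurality and deprivation with patient case-mix and discharging-hospital grade, but without the consensus score. Report this as the overall rurality effect. Hospital grade must stay, or the comparison would mix a change in confounder control with the removal of the mediator.
3. As a sensitivity choice, repeat this without team size.
4. Keep the model already described for the adoption effect, and label its rurality term as the effect at a fixed service model.
5. Describe how the consensus score varies with rurality across teams.
6. Do not interpret the difference between the two rurality coefficients as an indirect effect if rurality-by-score interaction is present. The framework expects context and mechanisms to interact. Unmeasured common causes of score and outcome would also invalidate that reading.

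The cost is one extra model and one table column per outcome on the same data, plus one further run per outcome if the team-size sensitivity analysis is done.

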#### Site selection

This study is designed to investigate the impact of different models of ESD operating over defined geographical regions of the East Midlands, West Midlands, East of England, and North of England (clinical network boundaries). This will allow an investigation of the consequences of a Midlands and East initiative to implement ESD beginning in 2012 [25] contrasted with a region (North of England) that has been slower to implement ESD based on SSNAP post-acute organisational audit data [9]. Sites within each of the four regions will be defined according to Clinical Commissioning Group (CCG) and local authority boundaries. All individual ESD teams within each site that participate in the SSNAP clinical audit will be included.

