An additional analysis using a difference-in-difference, i.e. before-and-after design, will then be conducted to further investigate the magnitude of ESD impact on patient length of hospital stay [31]. This will provide a comparative analysis to the previous cross-sectional approach whereby we compare that 2015–2016 time period with a previous time period (2013–2014) in terms of ESD prevalence and its impact on inpatient length of stay across the two time periods. Difference-in-difference analysis enables investigation of differences in length of hospital stay over time and comparison between sites that have implemented ESD with sites that have not. To do this, the analysis requires use of data collected before and after the implementation of ESD. In this study, implementation of ESD is measured in terms of ESD being offered as part of the patients’ care pathway, from their admitting hospital and across the two time periods. Furthermore, we will determine which admitting hospitals had ESD as part of their care pathway at each time period, using patient-level SSNAP data, which tracks patient journey from first inpatient admission to final discharge destination.

### Work package 2

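### The team-level adjustment set names neither service age nor region, so the consensus-score association may be confounded by service maturity, with unknown direction and size

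*Protocol article*

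**What the plan says.** The protocol article (*Data collection and analysis*) sets a key aim of Work package 1: to "investigate whether the degree to which an ESD service has adopted an evidence-based model is related to better patient care", together with dependency. It says covariate adjustment will be used to approach the true effects of teams on their patients.

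The exposure is fixed in *Evaluating the effectiveness of ESD service provision*: "An ESD consensus score will be applied to each ESD team included in our multilevel modelling". The organisational information behind the score comes from the 2015 audit, and the patient data are from 2016. The same section introduces the other team variables with "Data variables at the ESD team level (in addition to the ESD consensus score) will include" and names rurality, deprivation and the grade of the discharging hospital, then adds a team-size score. Time since launch and region are not named. The reason given for including contextual variables is that they may vary between teams and may affect both provision and outcomes.

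On the regions, *Site selection* (Work package 1) says: "This will allow an investigation of the consequences of a Midlands and East initiative to implement ESD beginning in 2012", and that this is "contrasted with a region (North of England) that has been slower to implement ESD". On the teams: "All individual ESD teams within each site that participate in the SSNAP clinical audit will be included". No minimum operating time is stated.

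Timing of implementation is used elsewhere, in *ESD impact on patient length of hospital stay*: "we will determine which admitting hospitals had ESD as part of their care pathway at each time period, using patient-level SSNAP data". That analysis compares 2013–2014 with 2015–2016, is kept separate from the team data, and groups patients by admitting hospital.

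**The concern.** A service that has run for several years may be more complete on staffing, training and meetings. It may also respond faster or treat more intensively simply because its staff and referral routes have settled. If both hold, service age is a common cause of the score and the outcome. A model without it gives the score some of the credit that belongs to time in operation.

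Service age plausibly meets the plan's own reason for including contextual variables, and pace of implementation is the dimension on which the regions are contrasted. The score coefficient answers the main Work package 1 question. *Cost-consequence analysis* takes modified Rankin changes from a comparison of ESD model types as treatment effects, so a distortion could carry into it. *Impact* says the findings will influence commissioning.

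**Working it through.** **Is there a figure to reproduce?** No. The article states no number of teams, effect size or power for these models. The values below are assumptions that show how the size depends on two unknowns.

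**Do teams plausibly differ in age?** *Site selection* contrasts an initiative from 2012 with slower implementation. The difference-in-difference design needs some hospitals to have gained ESD between 2013–2014 and 2015–2016. Where a new team supplied that ESD, it was young in the 2015 audit and the 2016 patient data. Teams dating from 2012 or before would sit beside it. This is inference; no team ages are given.

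**Size on a standardised scale.** Let rho be the correlation of score with team age, and g the direct effect of team age on the team-mean outcome (SD per SD). With no true score effect and age left out:

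bias in score coefficient = rho × g

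This was checked by simulating team-level regressions (8,000 replicates per cell, two-sided 5% t test, true score effect zero), with 30 or 60 teams, rho from 0 to 0.6, and g of 0.2 or 0.4.

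| rho | g | rho × g | Simulated bias, 30 / 60 teams | Rejection rate, 30 / 60 teams |
|---|---|---|---|---|
| 0 | 0.2 | 0 | −0.007 / 0.001 | 4.8% / 4.7% |
| 0 | 0.4 | 0 | −0.004 / −0.001 | 5.2% / 4.8% |
| 0.2 | 0.2 | 0.04 | 0.041 / 0.042 | 5.3% / 6.4% |
| 0.2 | 0.4 | 0.08 | 0.079 / 0.080 | 6.9% / 9.5% |
| 0.4 | 0.2 | 0.08 | 0.079 / 0.085 | 7.0% / 10.4% |
| 0.4 | 0.4 | 0.16 | 0.157 / 0.160 | 13.4% / 23.8% |
| 0.6 | 0.2 | 0.12 | 0.123 / 0.118 | 9.8% / 15.1% |
| 0.6 | 0.4 | 0.24 | 0.238 / 0.241 | 24.6% / 46.4% |

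With age added, the mean bias lies between −0.007 and 0.005 and the rejection rate between 4.6% and 5.3% in every cell. Negative rho was not simulated; by the formula it reverses the sign of the bias. The simulation uses team means and omits the other covariates, so it shows the mechanism rather than predicting the study's result.

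**Size in days, for responsiveness.** Let p be the share of established teams, d the score gap between established and new teams (score SD = 1), and gamma the days by which established teams make first contact sooner. Then:

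bias per SD of score = gamma × p(1 − p) × d

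- p = 0.7, d = 0.5, gamma = 0.5: 0.5 × 0.21 × 0.5 = 0.053 day
- p = 0.5, d = 1, gamma = 1: 1 × 0.25 × 1 = 0.25 day
- d = 0 or gamma = 0: no bias
- p = 0.5, d = −1, gamma = 1: −0.25 day, so the score effect is understated

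**The case against.** The strongest reply has five parts.

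- **Slower may mean fewer services, not younger teams.** Areas without ESD contribute no teams to these models. A reader might infer that the regions were chosen so that teams differ in age, but the stated purpose is to study an initiative and contrast the pace of implementation. This stands against that reading. It does not show that teams are of similar age, and the difference-in-difference design expects some ESD pathways to be recent.
- **The direction is unknown.** A reader might infer that a learning effect will flatter the score. The article shows neither link that this needs. Teams set up after the consensus statements could adhere more closely than older ones, which would reverse the sign. This stands in full.
- **Maturity may act only through the scored components.** In that case there is no direct path and no bias. That is a condition on the concern, not an argument against adjusting: the path from age through score to outcome stays in the score coefficient when age is in the model.
- **Every team scored in the 2015 audit existed before the 2016 patient data.** This narrows the contrast, but a team in the 2015 audit may still be new.
- **The list is open and the article is condensed.** The wording allows further variables, and a fuller plan may hold them. That limits the force of the point, but the published list still does not put service age or region into the model.

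A reader might also infer that the length-of-stay analysis already supplies the variable. It does not. It classifies admitting hospitals, in an analysis separate from the team data; a hospital may refer to several teams, and a team may serve several hospitals.

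**Conclusion.** The point holds in limited form. The named team-level variables leave out service age and region although the sites contrast earlier with slower implementation, so the consensus-score association with all three outcomes may be confounded by service maturity.

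The article does not support a claim that the estimate is biased, or biased in the study's favour. Bias requires that maturity be related to the score and also affect the outcome other than through the score. If either fails, the bias is zero. At an assumed score–age correlation of 0.4 and an age effect of 0.2 to 0.4 SD, it is 0.08 to 0.16 SD, with false-positive rates of about 7–13% with 30 teams and 10–24% with 60. These figures are illustrations resting wholly on assumed inputs. The case for acting is that a check is feasible and concerns the estimate on which Work package 1 mainly rests.

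**What to change.** Prespecify a sensitivity analysis for the responsiveness, intensity and modified Rankin models. Refit each with one team-level maturity variable: whether the team, or the ESD pathway of its main referring hospitals, appears in the 2013–2014 patient-level SSNAP data. If this cannot be mapped to teams, use region. Report the score coefficient with and without the added variable, and say in the interpretation whether it moves.

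Costs:

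- A hospital-to-team mapping step, using the patient-journey records that the length-of-stay analysis already draws on.
- Possible misclassification, since a team that joined the audit after it launched would look newer than it is.
- One team-level degree of freedom, or up to three for four regions.
- Region is a coarser substitute: it leaves age differences within regions unadjusted and absorbs other regional differences, so a shift in the coefficient could not be put down to maturity alone.

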To fulfil the study’s aim, the formal theory needs to be refined and preliminary realist hypotheses developed, codified into CMO conjectures, and tested through data collection. We drew on the work of Dalkin et al. [22] who suggested that explicitly disaggregating mechanisms into resources and responses highlights the difference between the intervention and generative mechanisms and facilitates the formulation of CMO configurations. We conceptualised the evidence-based core components of ESD services as the programme resources, and we will seek to surface the perspectives and behaviours of actors and stakeholders (staff and patients) who are making ESD happen on the ground. As intended outcomes, we used the process and patient outcomes examined by clinical trials and the national stroke audit, but we also allowed for exploration of unintended outcomes, mainly through the qualitative component of the study. Table 1 presents an initial CMO framework, which we will use to configure our realist hypotheses and examples of initial plausible scenarios. This example explores how the rurality of the location of the ESD service may lead to a facilitatory or countervailing interaction with mechanisms to generate intended or unintended outcomes. These hypotheses will be put to test through data collection and analysis in order to fine-tune underpinning CMO configurations and increase our understanding of how these elements are related [13]. This approach will be compared to existing implementation research frameworks, acknowledging the dynamic nature between an intervention’s core components, actors delivering the intervention, and the context in which this takes place [12, 20].

**Table 1 Tab1:** Programme theory CMO framework

Context	Mechanisms (resources + responses)		Outcomes
Rurality of ESD service location	Eligibility criteria		Accelerated transfer of care from hospital to home
	Team composition		
Commissioning and financial arrangements	Whole time equivalent staff/patient ratio	Staff perspectives/behaviour	Rehabilitation delivery—responsiveness
ESD provider organisation	Stroke specialism and staff training	Patient perspectives/behaviour	Rehabilitation delivery—intensity of rehabilitation
Referring services characteristics and locations	Multidisciplinary team co-ordination (e.g. meetings)		Patient outcomes—recovery

Example of a facilitatory CMO with intended consequences

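### The 'team-size' covariate, read as worded, is an average contract fraction and not a measure of team size; on no reading is it scaled to caseload

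*Protocol article*

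**What the plan says.** The protocol article, under 'Evaluating the effectiveness of ESD service provision', lists the variables for the two-level patients-within-teams models. The team-level list opens with "Data variables at the ESD team level (in addition to the ESD consensus score) will include level of rurality and deprivation" and goes on to the grade or score of each discharging hospital. A 'team-size' score is then added, defined as "total whole time equivalent (WTE) units per member of staff".

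The same section describes the 2015 organisational audit information to be collated on each service: "This will include ESD team composition, capacity, workload, and organisational features, e.g. frequency of team meetings". Team models are compared with consensus statements and guidelines, and "An ESD consensus score will be applied to each ESD team included in our multilevel modelling". The items of that score are not listed in the article.

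Under 'Conceptual framework', Table 1 names the staffing construct differently, as "Whole time equivalent staff/patient ratio", in the mechanisms (resources) part of the table. The text there says: "We conceptualised the evidence-based core components of ESD services as the programme resources".

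**The concern.** A score called 'team-size' should increase with the size of the team. The definition given is, on its face, a ratio with headcount in the denominator, and such a ratio removes size. An analyst who follows the text would put the average contract fraction into the model and report its coefficient under the name of team size.

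The variable is the only staffing covariate that the article names. Two of the outcomes are responsiveness (time from discharge to first contact) and rehabilitation intensity (treatment days over total days with ESD). How much staff time a team has for its caseload is a plausible reason for teams to differ on both. The plan aims to estimate the effects of teams with "covariate adjustments are made for a range of patient and ESD team characteristics", and it wants to relate outcomes to adoption of the evidence-based model. A staffing term that measures something else weakens that adjustment and invites a wrong interpretation of its coefficient.

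**Working it through.** The article gives no figure to reproduce here. The check is of what the definition measures.

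**Literal reading.** Let a team have *n* staff with contract fractions *f*₁ … *f*ₙ.

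- Total WTE = Σ*f*.
- WTE per member of staff = Σ*f* / *n*, the mean contract fraction.
- If every member works full time, Σ*f* / *n* = *n* / *n* = 1, whatever the value of *n*.

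**Illustration.** The teams below are hypothetical. Headcounts, contract fractions and annual caseloads are assumptions and are not taken from the document.

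| Team | Staff × fraction | Patients per year | Total WTE | WTE per staff member | WTE per 100 patients |
|---|---|---|---|---|---|
| A | 5 × 1.0 | 100 | 5 | 5/5 = 1.0 | 100 × 5/100 = 5 |
| B | 20 × 1.0 | 100 | 20 | 20/20 = 1.0 | 100 × 20/100 = 20 |
| C | 20 × 1.0 | 400 | 20 | 20/20 = 1.0 | 100 × 20/400 = 5 |
| D | 20 × 0.5 | 100 | 10 | 10/20 = 0.5 | 100 × 10/100 = 10 |
| E | 10 × 1.0 | 100 | 10 | 10/10 = 1.0 | 100 × 10/100 = 10 |

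- A, B, C and E all score 1.0 on the literal definition, although total WTE runs from 5 to 20 and WTE per 100 patients also runs from 5 to 20.
- D and E have the same total WTE (10) and the same WTE per 100 patients (10), but score 0.5 and 1.0.
- The order can also reverse. Three full-time staff score 3/3 = 1.00. Twenty staff at 0.6 WTE score 12/20 = 0.60, with 12/3 = 4 times the WTE.

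The literal score thus separates teams that do not differ in total WTE or in staffing per patient, and fails to separate teams that do. The particular figures are invented, but the invariance to size is algebraic.

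**Charitable reading.** If the phrase means WTE units added up over the members of staff, the score is total WTE: 5, 20, 20, 10 and 10 for A to E. That is a valid size measure. It still gives B and C the same value, though B has 20 and C has 5 WTE per 100 patients.

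**Against Table 1.** The construct there has patients in the denominator. Neither reading of the definition does. Of the other named team-level variables, rurality, deprivation and discharging-hospital grade are not staffing measures, and the content of the consensus score is not shown.

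**The case against.** **The phrase may simply mean total WTE.** The word 'total' and the label both point that way; on the ratio reading both would be idle. This stands as a reason not to claim that a contract fraction will in fact be modelled. It does not rescue the wording, because someone who applies the definition as written would compute the wrong variable.

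**A reader might infer that the models do not adjust for capacity.** The document does not support that. Capacity and workload are collated from the audit and compared with the consensus statements, the consensus score enters the models with items not listed, and the covariate list is introduced as what the data variables will include. The most that can be said is that no caseload-scaled covariate is explicitly named.

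**A reader might also infer that staffing is counted twice,** inside the consensus score and beside it. This is conjecture while the score's items are unknown, and the article may properly leave them to the full protocol. It is a reason for care in choosing the remedy, and no more.

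**Table 1 is an initial theory framework and not a covariate specification.** This is right. The plan nowhere says that the team-size score stands for the staff/patient row, and it would be coherent to adjust for size as context while treating the ratio as part of the intervention. The difference from Table 1 is therefore not a contradiction in itself. It shows only that the staffing construct named in the study's own theory has no explicit counterpart among the listed covariates.

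**Adding the ratio could over-adjust.** This stands too. If the ratio belongs to the evidence-based model, conditioning on it may take away part of the effect under study. Hence it belongs in a sensitivity model and should not replace the main specification.

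**Conclusion.** The point holds in a limited form. As worded, the definition of the 'team-size' score contradicts its label: total WTE over headcount is the mean contract fraction and says nothing about the size of the team. On the alternative reading it measures size but is not scaled to caseload. No named team-level covariate explicitly is, although responsiveness and intensity are outcomes and the study's theory names a staff/patient ratio.

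The conclusion about the label rests on the literal reading and on algebra alone; the team figures above only illustrate it. What the consensus score contains cannot be determined from the article, so neither unadjusted capacity nor double counting is established. The effect on any coefficient cannot be quantified from the document. The correction should be made because the error is specific and cheap to remove.

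**What to change.** 1. Redefine the 'team-size' score as total WTE per team, and drop the reference to members of staff.
2. Add a sensitivity model with WTE relative to patient caseload, where the audit workload data allow it. The article says that workload is collated but does not say that annual patient numbers are recorded, so the available denominator needs to be checked first.
3. Report the consensus-score coefficient with and without that term, and state whether the score already contains a staffing item. A reader can then judge how much of any change reflects confounding by staffing and how much reflects adjusting away a component of the evidence-based model.

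The cost is one redefined variable and one extra model run, using information that the plan already intends to collate.
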